#### **6.1.2. Description of the patient collective**

The patient population is identical in both study arms (biological / synthetic), as it is a self-controlled design. Therefore, the included patients are only described descriptively. For the hernias, however, specific details (size; side; pain) are recorded separately for both sides and compared according to the allocation.

#### 6.1.3. Primary outcomes

In this study, two primary endpoints are considered in parallel: pain intensity and recurrence. The total error of the first type ( $\alpha=0.05$ ) is distributed equally between the two endpoints according to a Bonferroni adjustment ( $\alpha=0.025$  in each case).

Pain intensity is recorded at 6 months after the operation using a visual analogue scale (VAS; 0-10 points) and tested for difference. Two pain values are recorded for each patient, separately for the left and right groin area. This means that dependent data is available. As experience shows that pain values are not symmetrically distributed, the evaluation is carried out non-parametrically with a rank test (Wilcoxon's rank sum test). The p-value is 0.025.

The second primary endpoint is the recurrence rate. The occurrence of a recurrence is recorded at several follow-up examinations over a period of 2 years after the procedure. A recurrence must be confirmed diagnostically. This endpoint will be tested for non-inferiority. It is expected that the recurrence rate with a biological mesh will be lower, the same or at most 3 % higher than the recurrence rate with a synthetic mesh. A range of  $\pm 3$  % is thus defined as still comparable. A 95 % confidence interval is determined for the observed difference in recurrence rates (biological - synthetic). If the value of  $+3$  % is not within this confidence interval, the biological mesh is considered non-inferior. Non-inferiority is a one-sided question. The 95 % confidence interval here corresponds to a one-sided question with a p-value of 2.5 %, as required by the Bonferroni correction.

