**Primary endpoint efficacy:**

All endpoints are analysed in the intention-to-treat population. In the absence of follow-up examinations, the LOCF (Last Observation Carried Forward) principle is used. Two primary endpoints are analysed (recurrence and pain); the p-value is adjusted according to Bonferroni. Pain reduction is determined separately for each side. The pain analysis is performed using the Wilcoxon signed-rank test for paired samples (alpha 0.025, two-sided). The evaluation of the recurrence rate requires a minimum observation period of 2 years. The difference in recurrence rates is expressed as a 95 % confidence interval (one-sided).

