#### 4.6.3. Method for assigning patients to the treatment groups and blinding

All patients included in the study are assigned a unique patient identifier. This consists of the abbreviation of the trial centre and the consecutive number of the included patient. As all included patients have a bilateral hernia, the randomisation only has to determine which side is operated on and how. The patient is therefore represented in both study groups, with one hernia in each study arm. Randomisation is therefore only between the following two options: "Right side biological and left side synthetic mesh" and "Left side biological and right side synthetic mesh".

Before the start of the study, the biometrician creates a randomisation list for each centre, which assigns the mesh material to the respective treatment side (right/left). Randomisation is stratified by centre and performed as block randomisation (block size 6-10). The randomisation results are announced centrally by telephone by the secretariat of the LKP in Cologne-Merheim ([name]) during regular working hours (elective procedure) in order to monitor the

progress of the study permanently and to be able to unblind the patient in the event of a recurrence (see below). The person entrusted with this task is not involved in the further steps of the study (e.g. follow-up).

As the surgical technique is identical for both sides, it is not possible to be unblinded from the outside by different scars or dressings postoperatively. Both the patient and the hospital staff (except the surgeon) are therefore blinded.

The surgeon cannot necessarily be blinded. Therefore, the follow-up should not be carried out by the surgeon (possibly by someone else from the surgical team).

In the event of a hernia recurrence that necessitates a reoperation, the affected side is unblinded by telephone by the LKP secretariat to enable adequate preparation for the operation. This automatically unblinds the unaffected side as well. When a hernia occurs, the study endpoint is reached for this hernia, but not for the patient. As long as the other side has not yet developed a recurrence, the patient remains in the study with the other hernia. Only when the other hernia also develops a recurrence is this patient's participation in the study terminated.

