#### *4.9.1.2. Preoperative preparation (D-3 bis D-1)*

- Pain according to VAS (0-10) separated by side
  - At rest
  - Under strain (coughing/pressing)
- Information/consent

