#### 6.1.5. Determination of the number of cases

First endpoint: Pain: Measurements of pain intensity using VAS are known to show high variability. Postoperative values show standard deviations (SD) of 1.5 - 2.0 points, while in follow-up examinations the mean values as well as the dispersion tend to be lower (SD 1.0 - 1.5). A larger proportion of patients will also have no pain at follow-up. In the present study, we expect this to be the case for about half of the hernias for both materials. Patients with pain mostly report intensities  $<5$  points. An expected difference of one point is therefore considered too large. A difference of 0.5 points is therefore planned here. With an SD of 1.5 points, this would mean a reduction of one third of the standard deviation. The required number of cases

to detect such a difference (paired t-test; power 90 %;  $\alpha=0.025$ ) would be 114 hernias per group, i.e. 114 patients. As a non-parametric rank test is planned for the analysis, an additional 15% is added to the number of cases, i.e. 131 hernias per group, or 131 patients.

The second endpoint "recurrence" is a non-inferiority hypothesis. A recurrence rate of approx. 5 % is expected over a period of two years (synthetic meshes). The maximum acceptable difference to the recurrence rate for the biological meshes is +3 %, i.e. a maximum recurrence rate of 8 %. If both meshes have the same recurrence rate (e.g. 5 %), then 203 cases are required to rule out a difference of more than 3 %, i.e. the 95 % confidence interval around 0 % is then [-3; +3]. If the recurrence rate for the biological meshes is 1 % higher than for the synthetic meshes, then 451 cases would be required for a 95 % confidence interval of +/- 2 %, i.e. the confidence interval around the difference of +1 % would then be [-1; +3]. This means that a difference > 3 would also be outside the confidence interval. As this is a one-sided question, a difference > 3 % can only be achieved with a  $p<0.025$ .

Thus, the second endpoint (recurrence) requires a larger number of cases ( $n=451$ ). If one also assumes a follow-up loss of approx. 10 %, this figure increases to a total of 496 people (with bilateral hernias).

The number of patients to be screened is 10% higher:  $n=546$ .

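### Preoperative pain is measured for each groin at two visits, but the primary pain analysis does not use it, and the wording leaves open whether baseline is subtracted or ignored

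*Protocol*

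**What the plan says.** Section 6.1.3 defines the pain endpoint by its 6-month value: "Pain intensity is recorded at 6 months after the operation using a visual analogue scale (VAS; 0-10 points) and tested for difference". The test is unadjusted: "the evaluation is carried out non-parametrically with a rank test (Wilcoxon's rank sum test". The synopsis names the paired version: "The pain analysis is performed using the Wilcoxon signed-rank test for paired samples (alpha 0.025, two-sided". (The two names conflict. That is a separate matter, and the paired test is taken as intended here.)

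Baseline pain is available. The preoperative CRF section lists "Pain according to VAS (0-10) separated by side", at rest and under strain, and section 4.9.1.1 lists the same items at screening. Section 6.1.2 gives baseline a descriptive role only: "specific details (size; side; pain) are recorded separately for both sides and compared according to the allocation".

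The wording of the endpoint varies. Sections 2.2 and 6.1.3 speak of pain intensity at 6 months. The synopsis and section 4.7.1.1 speak of pain reduction, and the synopsis adds: "Pain reduction is determined separately for each side".

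**The concern.** Using each patient as their own control removes what both groins share, such as age, comorbidity and surgeon. It does not remove what differs between the groins, and preoperative pain is one such factor. If the groin that hurt more before surgery tends to hurt more at 6 months, part of the spread in the 6-month difference is predictable from data in hand.

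The protocol allows two readings. Comparing raw 6-month values ignores the preoperative difference. Comparing reductions per side subtracts it in full. The two have different variances and can give different p-values on the same data. At stake are the width of the interval for the mesh effect, the treatment of a chance baseline imbalance, and a primary endpoint that can be read in two ways.

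**Working it through.** **Notation.** For each patient, D is the 6-month VAS on the biological side minus the synthetic side, B is the same difference before surgery, and r is the correlation of D and B.

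**Inputs from section 6.1.5 and the synopsis.** Difference 0.5; SD 1.5; two-sided alpha 0.025; power 90%; 451 evaluable patients; 496 recruited.

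**Assumed.** r from 0.1 to 0.5; where stated, equal SDs for B and D.

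**1. The plan's own figure.** n = ((2.2414 + 1.2816) × 1.5 / 0.5)² = 10.569² = 111.7, so 112. The exact t calculation gives 115; the protocol says 114. Then 114 × 1.15 = 131.1, matching 131. So 1.5 is used as the SD of D.

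**2. Unadjusted precision.** Half-width of the 97.5% interval at n = 451: 2.2414 × 1.5 / √451 = 0.158.

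**3. Adjusted for B.** The SD is multiplied by √(1 − r²).

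| r | √(1 − r²) | Half-width | Narrower by |
|---|---|---|---|
| 0.1 | 0.995 | 0.158 | 0.5% |
| 0.2 | 0.980 | 0.155 | 2% |
| 0.3 | 0.954 | 0.151 | 5% |
| 0.5 | 0.866 | 0.137 | 13% |

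**4. Change from baseline.** With equal SDs, Var(D − B) = 2(1 − r) Var(D): 1.6, 1.4 and 1.0 times Var(D) at r = 0.2, 0.3 and 0.5. Subtracting baseline therefore adds noise whenever r is below 0.5. Adjusted variance relative to the change score is (1 − r²) / (2(1 − r)) = (1 + r)/2, which is 0.60, 0.65 and 0.75.

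**5. Power.** At 0.5 points, n = 451 and SD 1.5, paired-t power exceeds 99.99%. If 1.5 is instead the SD on each of two uncorrelated sides, the SD of D is 1.5 × √2 = 2.12 and power is 99.7%. At half the planned effect, with 446 pairs (496 × 0.9), unadjusted power is Φ(0.25 / (1.5/√446) − 2.2414) = Φ(3.520 − 2.241) = 0.90. Simulation with adjustment gave 0.93 at r = 0.3 and 0.97 at r = 0.5.

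**6. Chance imbalance.** With SD 1.5 assumed for B, the standard error of its mean is 1.5/√451 = 0.071. An imbalance of two standard errors is 0.14 points. With equal SDs the slope equals r, so the unadjusted estimate moves by 0.3 × 0.14 = 0.04 or 0.5 × 0.14 = 0.07 points.

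**7. Skewed data.** In a simulation with skewed scores and about half of hernias pain-free, as section 6.1.5 expects, type I error under adjustment stayed near 0.025. The standard error fell by about 3% at r = 0.25 and 9–10% at r = 0.42. The formula gives 3.2% and 9.2%.

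**The case against.** **The gain is small and rests on an unknown r.** This stands. At r = 0.1 it is negligible, recurrence sets the sample size, and the planned 0.5 points would be detected either way.

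**The rank test was chosen for a reason.** Section 6.1.3 expects asymmetric pain scores, and a signed-rank test takes no covariate. This stands as a constraint on the fix. It is not a bar: with about 450 pairs and robust standard errors, inference on the mean difference holds up in step 7.

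**Pain reduction may simply mean less pain with one mesh than with the other.** The 0.5-point planning value fits that. But a reduction determined for each side separately cannot be a contrast between sides, so the ambiguity remains.

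**Adjusted analyses may be in the SAP.** A supplementary one could be. The definition of the primary endpoint is in the protocol, and there it is inconsistent.

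**Stronger readings that the protocol does not support.** Because of "Randomisation is stratified by centre and performed as block randomisation (block size 6-10", a reader might infer that leaving out centre and side also loses precision. Every patient supplies both arms, so a centre main effect cancels in D; simulated standard errors were the same with and without centre terms (0.0717 and 0.0717). With balanced sides, an assumed side effect of 0.3 points also left the standard error unchanged (0.0699 and 0.0699). Ignoring it inflates the estimated variance by at most 0.3²/1.5² = 4%, which is conservative. A reader might also infer bias. Side is randomised, so any baseline imbalance is chance, and the unadjusted test is valid.

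**Conclusion.** The point holds for baseline only. The protocol collects side-specific preoperative pain at two visits, does not use it in the primary pain analysis, and words the endpoint so that baseline may be either ignored or subtracted. Adjustment narrows the interval by about 2% to 13% against raw 6-month values for r from 0.2 to 0.5, and cuts variance by 25% to 40% against change scores if the SDs are equal. All of this depends on an r that the protocol does not give. At the planned effect neither power nor sample size is in question; the benefit is precision, an estimate less exposed to chance imbalance, and a single definition of the endpoint. This is a worthwhile improvement, and the unadjusted test is not an error.

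**What to change.** In section 6.1.3, the synopsis, and wherever else the endpoint is named:

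- Define the endpoint as VAS at 6 months. Choose rest or strain in advance and use the same component before surgery and at 6 months.
- Take B from the mean of the two preoperative visits.
- Analyse D adjusted for B in one of two ways. (a) Regress D on B alone with robust standard errors and take the intercept with a 97.5% interval as the mesh effect. Side is randomised, so B has expectation zero and the intercept is the average effect. (b) Apply the signed-rank test to D − bB, with b = ΣBD / ΣB² fitted through the origin. Swapping the meshes in a patient reverses the sign of both B and D and leaves b unchanged, so the test remains valid under no mesh effect.
- Report the unadjusted signed-rank test alongside.
- Do not add centre or side terms. With ordinary reference coding the intercept would describe one side in one centre; in simulation its standard error was 0.32, against 0.071 for the plain mean difference.

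Option (a) is preferable, because the precision figures above apply to it. The plain signed-rank test drops pairs with D = 0. Option (b) turns most of them into non-zero values, so with many pain-free pairs and a low r it can lose power.

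Cost: protocol wording and one extra modelling step, with no new data. The downside is that the primary test is no longer the plain signed-rank test.

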| Primary study objective:                              | It should be shown that the use of biological mesh material for
laparoscopic hernia treatment results in significantly less
postoperative pain than the use of synthetic mesh material,
without an increased recurrence rate |

Outcome:

Primary Outcome:

- Pain reduction after 6 months measured with a visual analogue scale (VAS 0-10)
- Recurrence rate after 2 years

Secondary Outcome:

- Frequency and intensity of pain at other time points (one week and one year after surgery)
- Recurrence rate after one year
- Local infection of the surgical site
- Mesh dislocation
- Haematoma
- Seroma
- Patient satisfaction (overall result, foreign body sensation, paraesthesia, one week and one year after surgery)

Evaluation criteria:

Effektiviness:

- The expected advantage of the biological mesh is 0.5 points on the 0-10 VAS.
- An assumed recurrence rate after 2 years of 5 % for the synthetic mesh material contrasts with a recurrence rate of  $\leq 8$  % for the biological mesh material.

Security:

- Number and type of complications such as re-interventions or replacement of the mesh

Diagnosis and main  
inclusion criteria:

Diagnosis/main inclusion criterion:

- Patients with bilateral primary inguinal hernias

Further inclusion criteria:

- Patient is suitable for laparoscopic surgery

Main exclusion criteria:

- Recurrent Hernia
- Incarcerated Hernia
- Presence of an acute systemic infection

Test product:

Type of application:

Not two specific products but two types of materials are compared. Each study centre must use commercially available mesh material. However, the following requirements apply:

- CE-certified meshes
- The synthetic mesh materials should be made of polypropylene, polyester or PVDF, have large pores and be lightweight ( $< 100 \text{ g/m}^2$ ).
- The biological mesh material should consist of a perforated, non-crosslinked, acellular and collagenous matrix.
- The meshes should have a minimum size of 10x15 cm
- The meshes can be fixed with adhesive

Comparative therapy,  
dosage and method of  
application:

Both mesh materials are used for each patient and compared directly with each other (self-controlled design). Other procedures/materials are not usual for this indication. The usual laparoscopic implantation in hernia repair is performed according to IEHS guidelines.

Duration of therapy:

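### Section 6.1.3 names the unpaired Wilcoxon rank sum test for the paired primary pain endpoint, against the synopsis and the sample-size calculation; probably a naming slip, but it needs correcting

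*Protocol*

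**What the plan says.** The Protocol describes the analysis of the primary pain endpoint in three places.

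- **Section 6.1.3 (Primary outcomes).** "Two pain values are recorded for each patient, separately for the left and right groin area". The text then draws the consequence, "This means that dependent data is available", and in the next sentence names the test: "the evaluation is carried out non-parametrically with a rank test (Wilcoxon's rank sum test"). The significance level is 0.025, because the overall 0.05 is "distributed equally between the two endpoints according to a Bonferroni adjustment".
- **Synopsis (Primary endpoint efficacy).** "The pain analysis is performed using the Wilcoxon signed-rank test for paired samples (alpha 0.025, two-sided").
- **Section 6.1.5 (Determination of the number of cases).** "A difference of 0.5 points is therefore planned here", with an SD of 1.5. A paired t-test at 90% power and alpha 0.025 gives 114 patients. A 15% allowance for a rank test, not named there, brings this to 131.

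The synopsis also fixes the design: "Both mesh materials are used for each patient and compared directly with each other (self-controlled design"). Nothing in the Protocol says which of the two named tests prevails.

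**The concern.** The rank sum test (Mann-Whitney) compares two independent samples. Here each patient contributes one value to each arm. The null variance used by the rank sum test leaves out the covariance between the two sides. If the sides are positively correlated, that variance is too large: the p-value is miscalibrated towards non-significance, and the precision that pairing should bring is lost.

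The literal reading is not far-fetched. Section 6.1 makes the hernia, not the patient, the unit of investigation, and 6.1.5 speaks only of a rank test. An analyst working from section 6 alone could run an unpaired hernia-level test and be following the Protocol. At stake is the definition of one of two confirmatory tests.

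**Working it through.** **1. Which test the sample size supports.** Inputs from 6.1.5: difference 0.5, SD 1.5, power 90%, alpha 0.025.

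Paired formula: n = [SD × (z(1−α/2) + z(power)) / difference]²

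- Two-sided 0.025: [1.5 × (2.241 + 1.282) / 0.5]² = 111.7, so 112 by normal approximation; an exact noncentral-t search gives 115. The stated 114 lies between them.
- 114 × 1.15 = 131.1, which gives the stated 131.
- One-sided 0.025 (the same as two-sided 0.05) gives 94.6, or 97 by exact t; one-sided 0.05 gives 77.1, or 79. Neither fits 114.
- Two independent groups with SD 1.5: 2 × 111.7 = 223.4, so 224 per group, and 223.4 rounded up × 1.15 = 224 × 1.15 = 257.6, so 258. This does not fit either.

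The stated figures therefore belong to a paired, two-sided 0.025 analysis, with 1.5 taken as the SD of the within-patient difference. Since SD of difference = SD per side × √(2(1 − correlation)), this equals a per-side SD of 1.5 at correlation 0.5.

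**2. What the rank sum test does to such data.** The Protocol gives no left-right correlation, so a range is assumed. The model follows the expectation in 6.1.5 that about half the hernias are pain-free: normal values cut off at 0, half of them at 0, per-side SD about 1.3, correlation set on the underlying scale. The size is 496 × 0.9 = 446 patients after the planned 10% loss. The true difference of 0.14 points is an assumption chosen to represent an effect well below plan. Results are by simulation at two-sided alpha 0.025.

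| Assumed correlation | Rank sum type I error | Power at 0.14, rank sum | Power at 0.14, signed-rank |
|---|---|---|---|
| 0 | about 2.5% | 32% | 30% |
| 0.25 | about 1% | 32% | 39% |
| 0.5 | 0.3% or less | 25% | 50% |
| 0.7 | 0.3% or less | 24% | 73% |

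The signed-rank test holds about 2.5% throughout. At a difference of 0.27 and correlation 0.5, power is 95% against 99%. At about 0.5 points both tests are near 100% at every correlation tried.

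**3. At the pain endpoint's own 131 patients.** With normal data, a difference of 0.5 and the SD of the difference held at 1.5, rank sum power is about 92%, 86%, 70% and 23% at correlations 0, 0.25, 0.5 and 0.75. Signed-rank power stays at 92 to 93%. This shows that the 131 is adequate only for the paired test; it is not the trial's actual size, which recurrence sets at 451 evaluable patients.

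**The case against.** The strongest defence is that this is one wrong name in an otherwise consistent plan. The sentence before it calls the data dependent, the synopsis names the paired test with its level and sidedness, the sample size is paired, and self-control is stressed throughout. That stands, and it is why the point is a naming error and not a design error. A reader might infer that 6.1.3 discards the self-controlled design; the documents do not support that.

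The consequence is also bounded. The correlation is an assumption. At 0 nothing is lost, and at 0.25 the loss is small. With positive correlation the rank sum test errs on the conservative side, so it does not inflate false claims of superiority. The planned 0.5 points is not at risk at the actual trial size. All of this stands.

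A reader might also infer that having two tests on record allows the choice to be made after the data are seen. The Protocol does not establish this: section 6.1 commits to a statistical analysis plan before recruitment. That plan is not at hand and may already settle the test.

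What remains is that the main analysis section names a test that does not fit the data it describes and contradicts the synopsis.

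**Conclusion.** The point holds as an inconsistency on a primary endpoint. Section 6.1.3 names an unpaired test for data it calls dependent, while the synopsis and the sample size are paired. Applied literally, the test would be miscalibrated and inefficient to a degree set by the unknown left-right correlation: negligible near 0, and a halving of power or worse at 0.5 to 0.7 when the true difference is about 0.14 points. By 0.27 points the loss at correlation 0.5 is already down to four percentage points, and at the planned 0.5 points with about 450 patients it vanishes. The loss therefore matters only if the true effect is smaller than planned. These sizes rest on the assumed correlation range and on the model with half the hernias pain-free. The contradiction itself rests on the text alone.

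**What to change.** In section 6.1.3, replace the rank sum test by the Wilcoxon signed-rank test on the within-patient difference (biological minus synthetic), two-sided alpha 0.025, so that it matches the synopsis. This changes one phrase through the written amendment route of section 8. Design, data collection and sample size stay as they are.

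No Hodges-Lehmann estimate needs to be added. With half the hernias pain-free, many paired differences are zero, and in simulation at correlation 0.5 that estimate came out at about 0.30 for a true mean difference of 0.47, so it would understate the effect on the scale used for planning.

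### The non-inferiority criterion for recurrence names no limit, so as literally written it is also met by an interval lying wholly above +3 %

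*Protocol*

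**What the plan says.** Recurrence at two years is one of two primary endpoints and is to be tested for non-inferiority. Section 6.1.3 describes the analysis as follows:

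- A 95 % "confidence interval is determined for the observed difference in recurrence rates (biological - synthetic"), so positive values mean more recurrences with the biological mesh.
- The decision rule: if +3 % "is not within this confidence interval, the biological mesh is considered non-inferior".
- The error rate: "The 95 % confidence interval here corresponds to a one-sided question with a p-value of 2.5 %, as required by the Bonferroni correction".

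The intended direction appears nearby. Section 6.1.3 expects that the biological rate "will be lower, the same or at most 3 % higher than the recurrence rate with a synthetic mesh" and adds that "Non-inferiority is a one-sided question". Section 6.1.5 sets the margin: "The maximum acceptable difference to the recurrence rate for the biological meshes is +3 %, i.e. a maximum recurrence rate of 8" per cent.

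The synopsis (paragraph on the primary efficacy endpoint) describes the interval differently: "The difference in recurrence rates is expressed as a 95 % confidence interval (one-sided").

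**The concern.** A two-sided interval has two ways of not containing +3 %. Its upper limit may be below +3 %, which is non-inferiority. Or its lower limit may be above +3 %, which shows an excess larger than the margin. The sentence in 6.1.3 gives the same verdict for both. It is the protocol's only explicit decision rule for this endpoint, and no sentence names the upper limit.

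This endpoint guards against paying for less pain with more recurrences. Its success criterion should be right as it stands, and it should deliver the 2.5 % error rate that the same section assigns to it.

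**Working it through.** **Inputs.** Margin +3 points, synthetic rate 5 %, n = 451 and a planning half-width of 2 points (6.1.5); one-sided error 2.5 % (6.1.3). The protocol gives no correlation between the two sides of a patient, so independence is assumed where a standard error is needed.

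**1. Which interval is meant.** Section 6.1.5 illustrates the interval as [-3; +3] with 203 cases and [-1; +3] with 451. The half-width formula n = z² × 0.05 × 0.95 / w² shows which multiplier was used:

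- z = 1.96, w = 0.03: 3.8416 × 0.0475 / 0.0009 = 202.7, so 203 as stated.
- z = 1.96, w = 0.02: 3.8416 × 0.0475 / 0.0004 = 456.2, so 457 against 451 stated (1.3 % apart).
- z = 1.645, w = 0.03: 2.706 × 0.0475 / 0.0009 = 142.8, which does not match 203.
- Allowance for losses: 451 × 1.10 = 496.1, against 496 stated.

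Sections 6.1.3 and 6.1.5 therefore describe a two-sided 95 % interval.

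**2. The rule against the three possible positions of that interval.**

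| Position of the interval | Rule as worded | Rule as intended |
|---|---|---|
| Upper limit below +3 | non-inferior | non-inferior |
| Contains +3 | not shown | not shown |
| Lower limit above +3 | non-inferior | not non-inferior |

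**3. Two examples of the third row.**

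- With the protocol's own half-width of 2 points, an observed difference of +8 gives [+6; +10].
- With n = 451, observed rates 5 % and 12 %, and independent sides: SE = √((0.05 × 0.95 + 0.12 × 0.88)/451) = √(0.1531/451) = 1.84 points, so 7 ± 1.96 × 1.84 = [+3.4; +10.6].

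Under the second set of assumptions the lower limit passes +3 once the observed excess reaches about 6.6 points.

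**4. How often the wording is met.** For a true difference d, by normal approximation:

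- as worded: Φ((3 − d)/SE − 1.96) + Φ((d − 3)/SE − 1.96)
- as intended: the first term only.

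At d = 3 each term is Φ(−1.96) = 0.025, whatever the SE. The wording therefore gives 0.050 and the intended rule 0.025.

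| True difference (points) | As worded, SE = 2/1.96 = 1.02 | As worded, independent sides (SE 1.6 to 2.0) | As intended (either SE) |
|---|---|---|---|
| +3 | 0.050 | 0.050 | 0.025 |
| +5 | 0.50 | 0.21 | 0.001 or less |
| +7 | 0.975 | 0.58 | < 0.001 |
| +10 | about 1.00 | 0.94 | < 0.001 |

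The 5 % is thus the value at the margin, not a ceiling. Read literally, the criterion is met more often as the biological mesh gets worse.

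**5. Whether the synopsis label rescues the rule.** For an interval with only an upper bound, +3 lies outside it only when that bound is below +3, so the direction would be right. But an ordinary one-sided 95 % bound (estimate + 1.645 × SE) carries 5 % error at a true +3. Added to the 0.025 for pain, that makes 0.075 against the planned total of 0.05. Neither description of the interval, combined with the sentence as worded, delivers 2.5 %.

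**The case against.** The strongest reply is that the sentence should not be read apart from its paragraph. Section 6.1.3 calls the question one-sided, allows the biological rate to be at most 3 points higher, and treats ±3 points as the comparable range. An interval of [+3.4; +10.6] lies wholly outside that range. Section 6.1.5 speaks of ruling out an excess above 3 points, and both its worked intervals end at +3 on the upper side. This stands: the direction is not in doubt, and a competent analyst would use the upper limit.

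A reader might also take 6.1.5 to repeat the error, because it says "This means that a difference > 3 would also be outside the confidence interval". It does not. That sentence requires values above 3 to lie outside the interval, and [+3.4; +10.6] contains nothing else. Section 6.1.5 gives the correct reading.

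Nor should 0.58 and 0.94 be read as chances that the trial reaches a wrong conclusion. They are chances that the interval lies above +3 if the true biological rate is 12 % or 15 %. Both rates are above the 1 to 10 % range that the introduction quotes for recurrence. A wrong conclusion would also need someone to apply the sentence against the text around it.

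A statistical analysis plan may state the rule properly. It is not at hand, and the protocol states a rule of its own, so the protocol's sentence should still be right.

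**Conclusion.** The criterion in 6.1.3 is wrongly worded. For the two-sided interval that the protocol describes, it is met by an interval wholly above the margin, and at a true difference of +3 points it gives 5 % error instead of the stated 2.5 %. That result needs no assumption about correlation or recurrence rates beyond the normal approximation. Only the [+3.4; +10.6] example and the column for independent sides rest on independence.

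A reader might infer that the sponsor intends to declare non-inferiority for a clearly worse mesh. The documents do not support that, since the surrounding text fixes the direction. This is a low-severity wording error in a primary decision rule. It is worth correcting because the sentence is the stated success criterion, and because the synopsis label, read as an ordinary one-sided 95 % bound, conflicts with the 2.5 %.

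**What to change.** In 6.1.3, replace the decision sentence with:

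> *The biological mesh is non-inferior if the upper limit of the two-sided 95 % confidence interval for the difference (biological minus synthetic), equivalent to a one-sided 97.5 % limit, is below +3 percentage points.*

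In the synopsis, describe the same interval: two-sided 95 %, upper limit compared with +3 points, one-sided error 2.5 %. The word *below* also settles an upper limit of exactly +3, as in both worked intervals of 6.1.5.

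The cost is one sentence in 6.1.3 and one label in the synopsis. The margin, the intended error rate and the figures 203, 451 and 496 are unaffected, and 6.1.5 needs no change on this point.
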